**Figure JPCE.7.1. Continued access diagram.**

Patients who are in short-term follow-up when the continued access period begins will continue in short-term follow-up until the 30-day short-term follow-up visit is completed. Long-term follow-up does not apply.

Patients who are in long-term follow-up when the continued access period begins will be discontinued from long-term follow-up.

## 8. Discontinuation Criteria

### 8.1. Discontinuation from Study Treatment

Patients will be discontinued from study treatment in the following circumstances:

- the patient is enrolled in any other clinical trial involving an investigational product or any other type of medical research judged not to be scientifically or medically compatible with this study
- the patient becomes pregnant during the study. See Section 9.2 regarding regulatory reporting requirements on fetal outcome and breastfeeding.
- the patient is significantly noncompliant with study procedures and/or treatment
- disease progression
  - Patients may remain on study treatment with repeat imaging >4 weeks to assess tumor response or confirmed progression per irRECIST to account for unique tumor response seen with immunotherapeutic drugs
- unacceptable toxicity
- the patient has had 1 dose reduction and experiences an AE that would cause a second dose reduction
- the patient, for any reason, requires treatment with another therapeutic agent that has been demonstrated to be effective for treatment of the study indication. Discontinuation from study treatment will occur prior to introduction of the new agent.
- the investigator decides that the patient should be discontinued from study treatment
- the patient requests to be discontinued from study treatment
- the patient's designee (for example, parents, legal guardian, or caregiver) requests that the patient be discontinued from study treatment

Patients who are discontinued from study treatment will have follow-up procedures performed as shown in the Schedule of Activities (Section 2).

For patients who discontinue study treatment without objectively measured progressive disease, continue to evaluate tumor response according to planned tumor assessment schedule by the same method used at baseline and throughout the follow-up periods until patient has objective disease progression or until the study's final analysis of OS. After the patient has objective disease progression, radiologic tests are no longer required.

#### 8.1.1. Discontinuation of Inadvertently Enrolled Patients

If Lilly or the investigator identifies a patient who did not meet enrollment criteria and was inadvertently enrolled, a discussion must occur between the Lilly CRP and the investigator to determine if the patient may continue in the study. If both agree it is medically appropriate to continue, the investigator must obtain documented approval from the Lilly CRP to allow the inadvertently enrolled patient to continue in the study with or without study treatment.

## 8.2. Discontinuation from the Study

Patients will be discontinued from the study in the following circumstances:

- participation in the study needs to be stopped for medical, safety, regulatory, or other reasons consistent with applicable laws, regulations, and good clinical practice (GCP)
- the patient becomes pregnant during the study. See Section 9.2 regarding regulatory reporting requirements on fetal outcome and breastfeeding.
- the investigator decides that the patient should be discontinued from the study
- the patient requests to be discontinued from the study
- the patient's designee (for example, parents, legal guardian, or caregiver) requests that the patient be discontinued from the study

Patients who discontinue from the study early will have follow-up procedures performed as shown in the Schedule of Activities (Section 2).

## 8.3. Lost to Follow-Up

A patient will be considered lost to follow-up if he or she repeatedly fails to return for scheduled visits and is unable to be contacted by the study site. Study site personnel are expected to make diligent attempts to contact patients who fail to return for a scheduled visit or who the site is otherwise unable to follow-up.

Study site personnel will attempt to collect the survival status for all enrolled patients who are lost to follow-up, including enrolled patients who do not receive study treatment, within legal and ethical boundaries. Public sources may be searched for survival status information. If the patient's survival status is determined, the survival status will be documented, and the patient will not be considered lost to follow-up.

Lilly personnel will not be involved in any attempts to collect survival status information.

## 9. Study Assessments and Procedures

Section 2 provides the Schedule of Activities for this study.

Appendix 3 provides a list of the laboratory tests that will be performed for this study.

Appendix 4 provides the schedule for collection of samples in this study.

Unless otherwise stated in the following subsections, all samples collected for specified laboratory tests will be destroyed within 60 days after receipt of confirmed test results. Certain samples may be retained for a longer period, if necessary, to comply with applicable laws, regulations, or laboratory certification standards.

### 9.1. Efficacy Assessments

Tumor response will be assessed every 6 weeks ( $\pm 7$  days) by investigator, with confirmatory assessment (including disease progression) obtained at the next routine scheduled imaging time point (that is, after 6 weeks  $\pm 7$  days). For the tumor expansion phase, after 48 weeks, tumor assessments will be conducted every 9 weeks. The same method of assessment and technique used at baseline should be used for each consecutive assessment thereafter.

See Section 10.3.2 for definitions of the efficacy endpoints.

#### 9.1.1. Appropriateness of Assessments

The measures used to assess safety and efficacy in this study are consistent with those used in most conventional oncology trials.

### 9.2. Adverse Events

The investigator will use Common Terminology Criteria for Adverse Events (CTCAE) Version 4.0 (NCI 2009) to assign AE terms and severity grades.

Investigators are responsible for:

- monitoring the safety of patients in this study and for alerting Lilly or its designee to any event that seems unusual, even if this event may be considered an unanticipated benefit to the patient
- the appropriate medical care of patients during the study
- documenting their review of each laboratory safety report
- following, through an appropriate health care option, AEs that are serious or otherwise medically important, considered related to study treatment or the study, or that caused the patient to discontinue study treatment before completing the study. The patient should be followed until the event resolves, stabilizes with appropriate diagnostic evaluation, or is reasonably explained. Frequency of follow-up evaluation is left to the discretion of the investigator.

Progression of the cancer under study is not considered an AE unless it is considered to be drug-related by the investigator.

After the ICF is signed, study site personnel will record via eCRF the occurrence and nature of each patient's preexisting conditions, including clinically significant signs and symptoms of the disease under treatment in the study. In addition, study site personnel will record via eCRF any change in the preexisting conditions and any new conditions as AEs. Investigators should record their assessment of the potential relatedness of each AE to study procedure or study treatment via eCRF. From the time of treatment allocation through 30 days following cessation of treatment, all AEs must be reported by the investigator.

The investigator will record all relevant AE/SAE information in the CRF.

The investigator will interpret and document whether or not an AE has a reasonable possibility of being related to study treatment or a study procedure, taking into account the disease, concomitant treatments, or pathologies. A "reasonable possibility" means that there is a cause and effect relationship between the study treatment and/or study procedure and the AE.

Planned surgeries and nonsurgical interventions should not be reported as AEs unless the underlying medical condition has worsened during the course of the study.

Study site personnel must report any dose modifications or treatment discontinuations that result from AEs to Lilly or its designee via eCRF, clarifying, if possible, the circumstances leading to the dose modification or discontinuation of treatment.

Adverse events meeting either of the below criteria, although not serious per International Council for Harmonisation (ICH) definition, are reportable in the same timeframe as SAEs to meet certain local requirements.

Therefore, these events need to be reported within 24 hours:

- is a new cancer (that is not a condition of the study);
- is associated with an overdose.

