## **7.4. Dosage Modification**

### **7.4.1. Special Treatment Considerations**

#### **7.4.1.1. Dose Adjustments and Delays**

Table JPCE.7.2 presents dose adjustments to occur if the event was related to abemaciclib. Any questions related to dose adjustments may be discussed with the Lilly clinical research physician (CRP).

Table JPCE.7.2. Toxicity Dose Adjustments and Delays of Abemaciclib

| Toxicity Type                                                                                                                                 | Toxicity Profile and Severity                                                                                                                              | Dose Suspension                                                                                                                                                        | Dose Reduction                                                                                                                       |
|-----------------------------------------------------------------------------------------------------------------------------------------------|------------------------------------------------------------------------------------------------------------------------------------------------------------|------------------------------------------------------------------------------------------------------------------------------------------------------------------------|--------------------------------------------------------------------------------------------------------------------------------------|
| Hematologic Toxicity
Section 7.4.1.1.1.1.1                                                                                                 | Grade 3                                                                                                                                                    | Dose MUST be suspended until toxicity resolves to at least Grade 2.                                                                                             | Dose MAY be reduced by 1 dose level - investigator's discretion.                                                              |

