#### **7.4.1.1.1.2. Nonhematological Toxicity**

Before the start of each cycle, nonhematologic toxicity (except alopecia and fatigue) possibly related to abemaciclib must resolve to either baseline or at least Grade 1. If a patient experiences  $\geq$ Grade 3 nonhematologic toxicity (except diarrhea, refer to Section 7.4.1.1.1.3; or ALT/AST increased, refer to Section 7.4.1.1.1.4; or ILD/pneumonitis, refer to Section 7.4.1.1.1.5; or VTE, refer to Section 7.4.1.1.1.6) possibly related to abemaciclib, then dosing must be suspended (until the toxicity resolves to either baseline or Grade 1) and the dose of abemaciclib must be reduced by 1 dose level as outlined in Table JPCE.7.2.

If a patient experiences persistent or recurrent Grade 2 nonhematologic toxicity (except diarrhea, refer to Section 7.4.1.1.1.3; or ALT/AST increased, refer to Section 7.4.1.1.1.4; or ILD/pneumonitis, refer to Section 7.4.1.1.1.5; or VTE, refer to Section 7.4.1.1.1.6) possibly related to abemaciclib that does not resolve with maximal supportive measures within 7 days to either baseline or Grade 1, then dosing must be suspended (until the toxicity resolves to either baseline or Grade 1) and the dose of abemaciclib must be reduced by 1 dose level as outlined in Table JPCE.7.2.

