### 7.7.1.2. Pembrolizumab

Patients should receive appropriate supportive care measures as deemed necessary by the treating investigator. Suggested supportive care measures for the management of AEs with potential immunologic etiology are outlined below. Where appropriate, these guidelines include the use of oral or intravenous treatment with corticosteroids as well as additional anti-inflammatory agents if symptoms do not improve with administration of corticosteroids. Note that several courses of steroid tapering may be necessary as symptoms may worsen when the steroid dose is decreased. For each disorder, attempts should be made to rule out other causes such as metastatic disease or bacterial or viral infection, which might require additional supportive care. The treatment guidelines are intended to be applied when the investigator determines the events to be related to pembrolizumab.

Note: If after the evaluation the event is determined not to be related, the investigator does not need to follow the treatment guidance (as outlined below). Refer to Section 7.4.1.1.2.2 for dose modification.

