### **10.3.3. Primary Outcome and Methodology (Safety and Tolerability)**

The primary objective is to evaluate safety and tolerability of abemaciclib in combination with pembrolizumab. All patients who receive at least 1 dose of study treatment will be evaluated for safety and toxicity. Adverse event terms and severity grades will be assigned by the investigator using CTCAE, Version 4.0.

Safety analyses will include summaries of the following:

- The CTCAE Version 4.0 term reported by the investigator will be mapped to the Medical Dictionary for Regulatory Activities (MedDRA) Preferred Term (PT) and System Organ

Class (SOC) using the corresponding MedDRA Lower Level Term (LLT), unless the reported CTCAE term is ‘Other – specify.’

- If the reported CTCAE term is ‘Other – specify,’ the MedDRA LLT, PT, and SOC centrally mapped from the verbatim AE term will be used.
- All listings and summaries will use the PT resulting from this process.

Preexisting conditions are defined as AEs that begin prior to the first dose of study drug.

A treatment-emergent adverse event (TEAE) is defined as an event that first occurred or worsened in severity after baseline. Comparisons of preexisting conditions to on-treatment events at the LLT level will be used in the treatment-emergent computation. The following summaries will be produced by PT within SOC: preexisting conditions, SAEs, TEAEs, drug-related TEAEs, and procedure-related TEAEs.

The following summaries will be produced by PT within SOC and maximum CTCAE grade: laboratory-based TEAEs, nonlaboratory-based TEAEs, drug-related laboratory-based TEAEs, and drug-related nonlaboratory-based TEAEs.

Reasons for death will be summarized separately for on-therapy and within 30 days of treatment discontinuation.

Hospitalizations and transfusions during the study treatment period or during the 30-day short-term follow-up period will be summarized by cohort.

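### Section 9.2 defines a reasonable possibility of relatedness as an actual cause-and-effect relationship, contradicting the possibility standard used elsewhere in the protocol

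*Protocol*

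**What the plan says.** Section 9.2 of the protocol makes three statements about causality.

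- The investigator is to "record their assessment of the potential relatedness of each AE to study procedure or study treatment via eCRF".
- The investigator is to interpret and document "whether or not an AE has a reasonable possibility of being related to study treatment or a study procedure", weighing the disease, concomitant treatments and other pathologies.
- The next sentence defines the key term. A reasonable possibility "means that there is a cause and effect relationship between the study treatment and/or study procedure and the AE".

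This is the protocol's only definition of the causality criterion.

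Other sections use a possibility standard without defining it. The text on nonhematologic toxicity applies to events "possibly related to abemaciclib, then dosing must be suspended", and the hematologic text is phrased the same way. Section 9.2.1 uses a reasonably-possibly-related or possibly-related test in three places: SAEs before the first dose, SAEs learned of after the patient has left the study, and SAEs caused by disease progression.

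Section 10.3.3 then plans summaries by preferred term within system organ class of "preexisting conditions, SAEs, TEAEs, drug-related TEAEs, and procedure-related TEAEs". It adds drug-related laboratory and nonlaboratory TEAEs by maximum grade.

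**The concern.** The instruction asks about a possibility, and the definition requires the relationship to exist. An event that the investigator thinks plausibly due to the drugs, but cannot attribute with confidence, is related under the instruction and unrelated under the definition. A word such as *may* appears to be missing.

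This matters because the trial's primary objective is safety and, as Section 5.4 says, there is no control population. Without a comparator, the investigator's causality call is the main device within the trial for separating drug effects from disease effects. A statistical analysis plan can tabulate those calls but cannot repair the criterion by which they were made. Where the call decides whether an event is collected at all, later analysis cannot recover the event.

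**Working it through.** No sample size, rate or power figure is involved, so the check is a comparison of texts followed by tracing where the relatedness call is used.

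**Step 1. Is the definition consistent with the rest?**

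| Place in the protocol | Standard stated |
|---|---|
| 9.2, instruction to the investigator | reasonable possibility |
| 9.2, eCRF recording | potential relatedness |
| 9.2, definition | the relationship exists |
| 7.4, hematologic and nonhematologic toxicity text | possibly related |
| 9.2.1, SAE before first dose | reasonably possibly related (to procedure) |
| 9.2.1, SAE learned of after leaving the study | reasonably possibly related |
| 9.2.1, SAE caused by progression | possibly related |

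Six of the seven entries use a possibility standard. Only the definition does not.

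**Step 2. Which uses depend on the definition?** A use is exposed when it relies on relatedness and states no standard of its own.

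- Drug-related TEAE summaries (10.3.3): no standard of their own, so exposed.
- SAEs in long-term follow-up (Table JPCE.2.3): only those related to regimen or procedure are collected, with no qualifier, so exposed. Section 9.2.1 separately requires all SAEs to be reported, related or not, for 90 days after treatment stops, or 30 days if new anticancer therapy starts. The exposure therefore falls mainly after that window.
- SUSARs (9.2.2): these depend on the investigator identifying the event as related, with no qualifier, so exposed.
- SAE reporting before the first dose, and the hematologic and nonhematologic dose-adjustment text: each states its own possibility wording and need not inherit the definition.

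**Step 3. Are the primary counts affected?** The endpoints in Table JPCE.4.1 are TEAEs, ECIs, SAEs, hospitalizations, laboratory tests, vital signs and physical examinations. Appendix 1 says a TEAE needs no causal relationship. ECIs (9.2.1.1) are defined by overdose or laboratory values. These counts do not use the call, with one narrow exception. Cancer progression counts as an AE only if considered drug-related (9.2), and SAEs caused by progression are reported only if possibly related (9.2.1). The all-causality counts are therefore largely, but not wholly, insulated.

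**Step 4. Size.** Let *p* be the share of events meeting the ordinary reasonable-possibility standard that are suspected but not established. Let *q* be the fraction of those that investigators classify by the literal definition. The proportional loss from the drug-related tables is *p* × *q*. If *q* = 0, the loss is 0. If *q* = 1, the loss is *p*. The protocol gives neither quantity, so only the direction (toward unrelated) and the limits (0 to *p*) can be stated.

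**The case against.** The strongest reply is that no experienced investigator would read the sentence literally. The operative question asks for a reasonable possibility, the recording instruction speaks of potential relatedness, and the neighbouring SAE text repeats the possibility standard. One badly worded sentence among several sound ones supports a risk of inconsistent reading, not a demonstrated bias. That stands. It is why the point is put as a risk and why the effect may be zero. It does not remove the defect, because the outlier is the sentence that purports to define the term.

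A reader might go further and infer that drug-related events are in fact under-counted, perhaps by a stated percentage. The documents do not support this. Any percentage would simply restate whatever value was assumed for *p*.

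A reader might also infer that relatedness is recorded only for the combination and so cannot be assigned to either drug. Section 9.2 names study treatment, but it does not say that this is the only attribution recorded, and the eCRF is not shown. Drug-specific judgments are required elsewhere: "Table JPCE.7.2 presents dose adjustments to occur if the event was related to abemaciclib", and the pembrolizumab supportive-care guidelines in Section 7.7.1.2 are "intended to be applied when the investigator determines the events to be related to pembrolizumab". AE-driven dose changes are also reported on the eCRF. The primary objective concerns the safety of the combination, so whether to tabulate by drug is a matter of detail or preference and not an error in this protocol.

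**Conclusion.** The definition in Section 9.2 contradicts the term it defines and the possibility wording around it, and it should be corrected. Followed literally, it would move suspected but unproven events out of the drug-related TEAE summaries, the related-only SAE collection in long-term follow-up, and SUSAR identification. The size is not derivable and ranges from nothing upward, depending on how investigators read the sentence. The all-causality TEAE and SAE counts are largely unaffected. The conclusion rests on the text alone and assumes that the uses without their own qualifier take their meaning from Section 9.2.

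**What to change.** Reword the opening of the defining sentence in Section 9.2 to: *A reasonable possibility means that there may be a cause and effect relationship, that is, there are facts or reasons to suspect one*. Leave the remainder, which names treatment, procedure and AE, as it is. This brings the definition into line with the instruction before it and with Sections 7.4 and 9.2.1. A broader test, under which any event that cannot be excluded counts as related, is not needed to resolve the contradiction and would be open to debate.

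The cost is one sentence. The downside is that somewhat more events may be labelled related. No endpoint or dose rule changes.

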### **9.2.1. Serious Adverse Events**

An SAE is any AE from this study that results in one of the following outcomes:

- death
- initial or prolonged inpatient hospitalization
- a life-threatening experience (that is, immediate risk of dying)
- persistent or significant disability/incapacity
- congenital anomaly/birth defect
- considered significant by the investigator for any other reason: important medical events that may not result in death, be life-threatening, or require hospitalization may be considered serious, based upon appropriate medical judgment.

Although all AEs after signing the ICF are recorded in the eCRF, SAE reporting begins after the patient has signed the ICF and has received study treatment. If an SAE occurs after signing the ICF, but prior to receiving study treatment, it needs to be reported ONLY if it is considered reasonably possibly related to study procedure.

Study site personnel must notify Lilly or its designee of any SAE within 24 hours of investigator awareness of the event via a Lilly-approved method. If alerts are issued via telephone, they are to be immediately followed with official notification on study-specific SAE forms. This 24-hour notification requirement refers to the initial SAE information and all follow-up SAE information.

For the time period beginning at treatment allocation through 90 days following cessation of treatment, or 30 days following cessation of treatment if subject initiates new anticancer therapy, whichever is earlier, any SAE, or follow up to a SAE, including death due to any cause other than progression of cancer, whether or not related to the study treatment, must be reported within 24 hours via a Lilly-approved method.

Pregnancy (during maternal or paternal exposure to study treatment) does not meet the definition of an AE but should be reported. To fulfill regulatory requirements, any pregnancy should be reported from the time of treatment allocation through 120 days following cessation of treatment, or 30 days following cessation of treatment if patient initiates new anticancer therapy, whichever is earlier, must be reported by the investigator to collect data on the outcome for both mother and fetus.

Investigators are not obligated to actively seek AEs or SAEs for patients once they have discontinued and/or completed the study (the patient summary CRF has been completed). However, if the investigator learns of any SAE, including a death, at any time after a patient has been discharged from the study, and he/she considers the event reasonably possibly related to the study treatment or study participation, the investigator must promptly notify Lilly.

Planned hospitalizations or procedures for preexisting conditions that were recorded in the patient's medical history at the time of enrollment should not be considered SAEs. Hospitalization or prolongation of hospitalization without a precipitating clinical AE (for example, for the administration of study treatment or other protocol-required procedure) should not be considered SAEs.

Serious adverse events, including death, caused by disease progression should not be reported unless the investigator deems them to be possibly related to study treatment.

